### General treatment regimen

Postoperative care is similar in both arms and based on enhanced recovery principles, which include early mobilization and expanding oral intake as desired by the patient. In the following sub-sections, we will clarify the recommendations for perioperative care. In case of radiological percutaneous drainage, amylase and culture must be determined in the drain fluid.

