**Methods/design:**

Binational multicenter randomized controlled non-inferiority trial, stratifying patients to high and low risk for POPF grade B/C and incorporating a standardized strategy for pancreatic transection. Two groups of 141 patients (282 in total) undergoing elective DP (either open or minimally invasive, with or without splenectomy). Primary outcome is postoperative rate of morbidity (Clavien-Dindo score ≥ 3), and the most relevant secondary outcome is grade B/C POPF. Other secondary outcomes include surgical reintervention, percutaneous catheter drainage, endoscopic catheter drainage, abdominal collections (not requiring drainage), wound infection, delayed gastric emptying, postpancreatectomy hemorrhage as defined by the international study group for pancreatic surgery (ISGPS) (Wente et al., Surgery 142:20–5, 2007), length of stay (LOS), readmission within 90 days, in-hospital mortality, and 90-day mortality.

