#### Prophylactic abdominal drainage

In the control arm, the abdominal drain will be placed intraoperatively when randomized into the drain group. In case of splenectomy, the drain is placed such that it includes the former splenic fossa with drain openings in this area and extending its tip until next to the pancreatic transection margin while avoiding direct contact with the splenic artery/vein stumps. The placed intra-abdominal drains are passive drains and will evacuate fluid by passive gravity, without active suction.

In the drain-group amylase levels are determined on day 1, 3, and 5 postoperatively (day 0 = day of DP). The drain can be removed on day 3 unless the drain levels exceed three times the upper limit of the institutions range of serum amylase (i.e., 2016 updated ISGPS definition of pancreatic fistula) or when the amount exceeds 200ml in 24h the fluid aspect is suspicious. This stands also for those patients in the no-drain group who, despite randomization, receive a percutaneous catheter drainage for any intraoperative reasons of concern.

For other details of the surgical procedure, surgeons can use a surgical technique according to his/her own preference as long as they use the same approach in all patients. All procedure details should be recorded within the case report form.

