## Methods

### Definitions

All definitions are displayed in the Additional file 1. The left pancreas is defined as the pancreatic portion (body and tail) located on the left side of the porto-mesenteric vein. Complications are classified according to the Clavien-Dindo score ≥ 3 [26]. Grade B/C POPF [19], delayed gastric emptying (DGE) [27], and postpancreatectomy hemorrhage (PPH) [18] are classified using the ISGPS definitions. Surgical site infection (SSI) is classified according to the Center for Disease Control and Prevention definition [28].

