#### Secondary parameters/endpoint

Secondary outcomes are grade B/C POPF, reoperation, catheter drainage, abdominal collections, wound infection, DGE, PPH, blood transfusion, length of stay (LOS), in-hospital mortality, 90-day mortality, readmission within 90 days, and start of adjuvant chemotherapy. Outcomes will be based on the Dutch Pancreatic Cancer Audit registry.Intraoperative parameters:° Date of operation;° Splenectomy;° Conversion;° Reason for conversion;° Vessel resection (excluding splenic vessels); if so, type of venous resection/reconstruction;° Operative time (from first incision to closure of the abdomen), minutes;° Intraoperative blood loss, mL (suction canister and weight of gauzes);° Intraoperative blood transfusion, mL fresh frozen plasma or packed cells.Postoperative parameters:° POPF (grade B/C)*;° Major complications (CD ≥ 3);° DGE (grade B/C)*;° PPH (grade B/C)*;° SSI*;° Postoperative intervention (radiology, endoscopy, surgery);° Reason for postoperative intervention.Hospitalization parameters:° LOS, days;° Readmission;° Intensive care admission;° Reason for intensive care admission;° Duration of intensive care admission, days;° CRP on 3rd postoperative day;° Amount of days with drain in place.See Additional file 1 for detailed definitions of study outcomes.

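### Fluid amylase is mandatory after radiological percutaneous drainage only, so grade B/C POPF may be under-ascertained in the no-drain arm

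*Protocol article*

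**What the plan says.** Under Prophylactic abdominal drainage, the protocol article schedules sampling in the control arm: "In the drain-group amylase levels are determined on day 1, 3, and 5 postoperatively (day 0 = day of DP"). The drain-removal rule that follows uses a threshold that the article identifies with the fistula definition: drain levels that "exceed three times the upper limit of the institutions range of serum amylase (i.e., 2016 updated ISGPS definition of pancreatic fistula"). It then adds: "This stands also for those patients in the no-drain group who, despite randomization, receive a percutaneous catheter drainage for any intraoperative reasons of concern".

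Under General treatment regimen, which applies to both arms, the one sampling rule for a postoperative intervention is: "In case of radiological percutaneous drainage, amylase and culture must be determined in the drain fluid".

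Other routes are foreseen. The abstract's secondary outcomes include surgical reintervention and "percutaneous catheter drainage, endoscopic catheter drainage", and Secondary parameters/endpoint records "Postoperative intervention (radiology, endoscopy, surgery"). The article attaches no sampling requirement to the endoscopic or surgical route.

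Under Definitions, POPF, delayed gastric emptying and haemorrhage "are classified using the ISGPS definitions", with the detail in Additional file 1. The sample size section calls grade B/C POPF the most relevant secondary endpoint, sizes it for non-inferiority with an 8-point margin at one-sided 2.5%, and sets the total at 282 so that both endpoints can support a conclusion.

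**The concern.** An endpoint compared for non-inferiority should be looked for equally hard in both arms. Here the laboratory value behind the fistula diagnosis becomes available in different ways. A drain-arm patient who later needs endoscopic drainage or reoperation should already have early amylase values from the operative drain. A no-drain patient with the same clinical course has no operative drain to sample, and the article does not require a test on the fluid removed at the intervention. Such an event could be recorded as a collection or a reintervention and not as grade B/C POPF.

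The direction matters. Missed fistulas in the no-drain arm lower its observed rate and make omission of the drain look safer, which is anti-conservative for non-inferiority. The Discussion already accepts that POPF B/C without intervention cannot be measured in the no-drain arm. Fistulas that lead to an intervention are what remains measurable there, so their ascertainment needs to be complete.

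**Working it through.** **1. Sampling by patient type, from the article's text**

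| Situation | Drain arm | No-drain arm |
|---|---|---|
| Operative drain in place | Amylase on days 1, 3 and 5 (removal possible on day 3) | Only if drained for an intraoperative concern; unclear whether the extension covers the sampling days or only removal |
| Later radiological percutaneous drainage | Amylase mandatory | Amylase mandatory |
| Later endoscopic drainage | Not required, but early drain values exist | Not required; usually no value at all |
| Reoperation | Not required, but early drain values exist | Not required; usually no value at all |

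The arms differ in the last two rows.

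**2. The plan's own POPF sample size**

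Inputs (Sample size calculation): success 75% with drain and 81% without, margin 8 points, one-sided 2.5%, power 80%.

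n per arm = (1.960 + 0.842)² × [0.75×0.25 + 0.81×0.19] / (0.08 + 0.06)² = 7.849 × 0.3414 / 0.0196 = 136.7, so 137 per arm and 274 in total. This matches the stated 274. Allowing 3% drop-out, 274/0.97 = 282.5, against the stated 282. No stated figure is wrong.

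**3. Illustration of one-sided under-ascertainment**

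Assumptions: drain-arm POPF 25% (from the plan); true no-drain POPF 33%, exactly on the 8-point margin; 137 per arm; a fraction f of no-drain fistulas left unclassified; no loss in the drain arm. The documents give no value for f and no split by drainage route.

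Observed no-drain rate: p = 0.33 × (1 − f).
SE = √{[p(1 − p) + 0.25×0.75] / 137}.
Probability of declaring non-inferiority = Φ[(0.08 − (p − 0.25)) / SE − 1.960].

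| f | p | Observed difference | SE | False non-inferiority |
|---|---|---|---|---|
| 0 | 0.330 | 0.080 | 0.0545 | 2.5% |
| 5% | 0.3135 | 0.0635 | 0.0542 | 4.9% |
| 10% | 0.297 | 0.047 | 0.0538 | 8.9% |
| 20% | 0.264 | 0.014 | 0.0528 | 23.9% |

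Worked line for f = 10%: (0.08 − 0.047)/0.0538 = 0.614; 0.614 − 1.960 = −1.346; Φ(−1.346) = 0.089.

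In patients: 0.33 × 137 = 45.2 true no-drain fistulas, so f of 5%, 10% and 20% means about 2, 5 and 9 missed.

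**4. If the loss were equal in both arms**

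With f = 10% in each arm the observed rates are 0.297 and 0.225, and the difference is 0.072. SE = √[(0.2088 + 0.1744)/137] = 0.0529. Then 0.008/0.0529 − 1.960 = −1.809, and Φ = 3.5%. The rise to 8.9% therefore comes mostly from the difference between arms.

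**The case against.** The strongest reply has four parts.

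First, the sampling sentence is not arm-specific. A drain-arm patient with low early values, a drain removed on day 3 and a late collection drained endoscopically has no required amylase on that fluid either. This stands. A reader might infer that fistulas are lost in one arm only, and the article does not support that. What remains is an imbalance: one arm has early values to fall back on and the other generally does not.

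Second, some no-drain patients are covered, because the drain-arm rule is extended to those drained for an intraoperative concern. This also stands, whatever the extension's exact scope, but it does not help a patient whose collection appears later.

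Third, the POPF definition sits in Additional file 1, endpoints are checked against primary sources by a blinded committee, reasons for intervention are recorded, and sites may test anyway. These are real safeguards, and misclassification is a risk that has not been shown to occur. However, neither a definitions file nor an adjudicator can supply a value that was never measured. The point does not rest on the article's silence: it states a mandatory rule and limits it to one route.

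Fourth, the Discussion gives unequal POPF measurement as the reason for choosing severe morbidity as primary. That is correct, and it confines the exposure to the secondary endpoint. A reader might infer that the trial's main conclusion is at risk. It is not, because Clavien-Dindo grade does not depend on amylase and the article lists reinterventions and catheter drainage among the primary events.

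**Conclusion.** The point holds as a gap in ascertainment for grade B/C POPF. The article mandates amylase for one of three intervention routes that it records, and the gap bears more heavily on the no-drain arm, in the direction that favours non-inferiority. It affects a secondary endpoint that the plan itself sizes for a non-inferiority conclusion. It does not affect the primary endpoint or any sample size figure.

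The size cannot be derived from the documents. The error rates of about 5%, 9% and 24% follow from assumed missed fractions of 5%, 10% and 20%, a true difference exactly on the margin and no loss in the drain arm. They show how sensitive the POPF comparison would be and do not estimate this trial's error. To be missed, a fistula must be treated by a non-percutaneous route, go untested and then be adjudicated as non-POPF. Any loss in the drain arm would reduce the effect.

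**What to change.** Extend the sentence under General treatment regimen so that amylase and culture are determined in fluid obtained by any postoperative route (percutaneous, endoscopic or surgical) in both arms.

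The new sentence cannot reach patients already treated; 152 of 282 were randomised when the article was submitted. For them, and for any later case with no amylase result on the intervention fluid, report a sensitivity analysis of grade B/C POPF. Count interventions for a collection at the transection margin first as POPF and then as non-POPF. Apply the rule identically in both arms, whatever the earlier operative-drain values; otherwise it would be triggered mainly in the no-drain arm. For the same reason, counting every untested collection as POPF should not be the main analysis, since it could bias the comparison the other way.

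The cost is one amended sentence, a laboratory test on fluid already being removed, and a small amount of extra analysis.

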### Use of co-intervention

There are no specific co-interventions.

## Methods

### Definitions

All definitions are displayed in the Additional file 1. The left pancreas is defined as the pancreatic portion (body and tail) located on the left side of the porto-mesenteric vein. Complications are classified according to the Clavien-Dindo score ≥ 3 [26]. Grade B/C POPF [19], delayed gastric emptying (DGE) [27], and postpancreatectomy hemorrhage (PPH) [18] are classified using the ISGPS definitions. Surgical site infection (SSI) is classified according to the Center for Disease Control and Prevention definition [28].

### Study parameters/endpoints

#### Main parameters/endpoint

Primary endpoint is the rate of Clavien-Dindo score ≥ 3 complications [26].

#### Secondary parameters/endpoint

Secondary outcomes are grade B/C POPF, reoperation, catheter drainage, abdominal collections, wound infection, DGE, PPH, blood transfusion, length of stay (LOS), in-hospital mortality, 90-day mortality, readmission within 90 days, and start of adjuvant chemotherapy. Outcomes will be based on the Dutch Pancreatic Cancer Audit registry.Intraoperative parameters:° Date of operation;° Splenectomy;° Conversion;° Reason for conversion;° Vessel resection (excluding splenic vessels); if so, type of venous resection/reconstruction;° Operative time (from first incision to closure of the abdomen), minutes;° Intraoperative blood loss, mL (suction canister and weight of gauzes);° Intraoperative blood transfusion, mL fresh frozen plasma or packed cells.Postoperative parameters:° POPF (grade B/C)*;° Major complications (CD ≥ 3);° DGE (grade B/C)*;° PPH (grade B/C)*;° SSI*;° Postoperative intervention (radiology, endoscopy, surgery);° Reason for postoperative intervention.Hospitalization parameters:° LOS, days;° Readmission;° Intensive care admission;° Reason for intensive care admission;° Duration of intensive care admission, days;° CRP on 3rd postoperative day;° Amount of days with drain in place.See Additional file 1 for detailed definitions of study outcomes.

#### Other study parameters

Other study parameters are baseline characteristics, including:Patient study identification number;Date of birth;Sex;Performance status (Karnofsky score)*;ASA physical status*;Body mass index (BMI), kg/m^2)^;Abdominal surgery in history;Diabetes mellitus;Diagnosis based on preoperative imaging.

*See Additional file 1 for detailed definitions of study outcomes.

### Randomization and treatment allocation

Eligible patients for the study will be identified at the outpatient clinic and in this stage informed consent will be obtained; the randomization will take place directly after start of the operation, when the decision is made to proceed with the resection. The surgeon performing the operation will call the study coordinator to perform the randomization in Castor EDC. Patients will be analyzed according to the allocated treatment, as per intention-to-treat principles. If during the operation is chosen not to act conform the randomization, specification of this choice is required. A per-protocol analysis will also be performed for the primary endpoint.

A data safety monitoring committee will assess safety endpoints per 50 randomized patients. All patients will be randomized centrally using an online computer-controlled permuted-block randomization module in a 1:1 ratio. The block sizes itself will be subject to random variation with block sizes varying from 4 to 8 patients. The entire randomization will be concealed to all involved investigators except the trial coordinators. Patients will be coded by a numeric randomization code and the principal investigator will be the only one with access to it and investigators and patients are not blinded. Patients will be stratified according to high or low risk and minimally invasive and open procedure. The source data will be stored digitally and will be kept by the project leader for 15 years after the inclusion of the last patient.

### Study procedures

#### Patient screening procedures

Screening of patients consists of standard procedures, including high-quality computed tomography (CT) of the pancreas. Screening procedures will be according to the local treating team’s preference.

#### Data collection

Baseline characteristics will be recorded before randomization. The required clinical data, i.e., primary and secondary outcomes, will be collected after randomization, i.e., from hospitalization up to 6 months postoperatively using standardized case report forms, and in Dutch centers according to the mandatory Dutch Pancreatic Cancer Audit which is coded. All complications will be scored using the Clavien-Dindo score of surgical complications (see Additional file 1).

#### Registration of patients not included in the PANDORINA trial

All patients undergoing elective DP but not included in the trial will be logged using a screening log. These patients will be registered anonymously using a standardized prospectively collected database. Due to this, it will be possible to assess the presence of patient selection by indication.

### Withdrawal of individual subjects

Subjects can withdraw from the study at any time for any reason if they wish to do so without any consequences. The investigator can decide to withdraw a subject from the study for urgent medical reasons.

### Replacement of individual subjects after withdrawal

Patients withdrawn after surgery will not be replaced. If a patient does not receive a resection due to intraoperative metastasis or other reasons for not performing a DP, he will not be randomized since the randomization process takes place only after the intention to resect. Patients withdrawn because of treatment-related reasons will not be replaced.

### Follow-up of subjects withdrawn from treatment

All subjects will be analyzed according to intention-to-treat principles and follow-up will be 6 months after DP.

## Safety reporting

### Safety reporting in the Netherlands

Safety reporting may be varying between participating centers or different countries. Sections below describe the details of safety reporting for Dutch medical centers.

#### Section 10 WMO event

In accordance to section 10, subsection 1, of the WMO, the investigator will inform the subjects and the reviewing accredited MEC if anything occurs, on the basis of which it appears that the disadvantages of participation may be significantly greater than was foreseen in the research proposal. The study will be suspended pending further review by the accredited Medical Ethics Review Committee, except insofar as suspension would jeopardize the subjects’ health. The investigator will take care that all subjects are kept informed.

#### AEs and SAEs

##### Adverse events (AEs)

Adverse events are defined as any undesirable experience occurring to a subject during the study, whether or not considered related to the placement of a drain after DP or not. All adverse events reported spontaneously by the subject or observed by the investigator or his staff will be recorded.

##### Serious adverse events (SAEs)

A serious adverse event is any untoward medical occurrence or effect that at any dose:Results in death;Is life threatening (at the time of the event);Requires hospitalization or prolongation of existing inpatients’ hospitalization;Results in persistent or significant disability or incapacity;Any other important medical event that may not result in death, be life threatening, or require hospitalization, may be considered a serious adverse experience when, based upon appropriate medical judgment, the event may jeopardize the subject or may require an intervention to prevent one of the outcomes listed above.

Predefined list of SAEs that will be reported to the study coordinator and CCMO:SAE resulting in mortality (for any reason);SAE necessitating surgical reintervention;SAE resulting in ICU admission.

The sponsor will report these SAEs through the preferred web portal to the accredited MEC that approved the protocol, within 15 days after the sponsor has first knowledge of the serious adverse events. SAEs that result in death or are life threatening will be reported expeditely. The expedited reporting will occur not later than 7 days after the responsible investigator has first knowledge of the adverse event. This is for a preliminary report with another 8 days for completion of the report. All SAEs will be reported until end of study. All participating physicians involved in the PANDORINA trial have to brief the study coordinator in case of mortality or any unexpected event that leads to a prolongation of the hospitalization or to readmission. Primary and secondary outcomes do not have to be reported immediately to the study coordinator. Mortality has to be reported by the attending physician to the study coordinator within 48 h after the occurrence.

The following SAEs are recorded in an overview list that will be submitted once a year to the MEC of the Amsterdam UMC, Amsterdam, the Netherlands. If mandatory, these SAEs are also reported to MECs of participating centers. These SAEs include, among others:Readmission;POPF grades B and C;PPH grades B and C;DGE grades B and C;Percutaneous catheter drainage.

#### Follow-up of adverse event

Follow-up for AEs will be at least up to 30 days after treatment. All AEs will be followed until they have abated, or until a stable situation has been reached. Depending on the event, follow-up may require additional tests or medical procedures as indicated, and/or referral to the general physician or a medical specialist. Common (serious) adverse events after pancreatic surgery, such as POPF, DGH and PPH will not be reported, as these complications occur in a large subset (>15–25%) of patients. Other adverse events will be reported until end of study, as defined in the protocol.

#### Data safety monitoring board

An independent data safety monitoring board (DSMB) will be appointed to evaluate the study safety parameters (all patients). After every 50 included patients, when 1 month of follow-up of these patients has passed, the DSMB will have a meeting and assess the safety parameters. This meeting may be a telephone or video conference. This DSMB will exist of one independent statisticians and two independent surgeons. One surgeon will be appointed as the DSMB chairman and a second member will act as secretary. The minutes of this meeting will be sent to the sponsor of the study by the study coordinator. The DSMB will not be blinded and fully informed on all SAEs. The DSMB can request a full report of specific study outcomes whenever required. The study coordinator and principal investigator will only be present during the start of the DSMB meeting to provide the data and provide background information. The result of the DSMB meeting will be sent to the trial steering committee, the sponsor of the study, and the Research Ethics Committee. Should the sponsor decide not to fully implement the advice of the DSMB, the authors will have to motivate their discussion for the Research Ethics Committee.

